## **11.4 Planned Analyses**

### **11.4.1 Datasets to be Analysed, Analysis Populations**

As recommended by the CONSORT statement (106), two analysis sets will be performed: per-protocol (PP) and intention-to-treat (ITT).

For PP analysis, we will exclude patients for the following reasons: patients who discontinue treatment prematurely (< 47 weeks), unless virological failure occurred before, patients with a treatment adherence of less than 80% while on treatment, those who do not have HIV-1 RNA results at week 48 (+/-21 days), unless virological failure occurred before, or patients with major protocol deviation(s) (i.e. any failure to obtain informed consent, violation of any inclusion criteria, not receiving the allocated treatment or monitoring). Per-protocol and intention-to-treat analyses should reach the same conclusion to consider DTG + FTC as non-inferior to standard treatment.

For ITT analysis, all randomized patients will be analysed in the allocated group regardless of any protocol violations.

All drop outs will be described and reasons for their discontinuation will be given where possible.

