|                                      | 
twice consecutively <math>\geq 100</math> copies/ml, this measure will be performed only on the sample with the highest value);
 
 
• Genotypic resistance in case of virological failure (defined as two HIV-RNA measurements <math>\geq 100</math> copies/ml 2 weeks apart);
 
• Pharmacogenetics analysis in case of virological failure (defined as two HIV-RNA measurements <math>\geq 100</math> copies/ml 2 weeks apart);
 
• Plasma samples will be stored at each study visit and used for dolutegravir and emtricitabine plasma concentration measurement, genotypic testing and pharmacogenetics analysis in patients with virological failure.
 
 
For patients in the standard monitoring arm, additional laboratory assessments will be performed as per SHCS regular assessments:
 
 
• Weeks 12, 24, 36: CD4 count, full blood count, safety serum chemistry, glucose and lipid profile.
 
 
Questionnaires: health-related quality of life and patient's monitoring satisfaction questionnaires will be performed for all patients at baseline and weeks 12 and 48.
                                                                                                                                                                                                                                                               |

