| Statistical Considerations: | 
DTG + FTC dual therapy is expected to be non- inferior to standard-of-care using a 12% non-inferiority margin assuming that 92% of patients are virologically suppressed at week 48 in the two comparison arms.
 
We will evaluate the proportion of patients with viral suppression at week 48 in each arm, and compute a Mantel-Haenszel risk difference (DTG+FTC minus cART) stratified by monitoring type with a two-sided 95% confidence interval. If the lower confidence limit is higher than -12% we will conclude non-inferiority. If the lower confidence limit is below -12% we will conclude that DTG + FTC is potentially inferior to cART. Per protocol (PP) and intention-to-treat (ITT) analyses will be performed. Exclusion criteria for PP will be: patients who discontinue treatment prematurely for reasons other than death, patients with a treatment adherence of less than 80%, or those who do not have HIV-1 RNA results available at week 48. For ITT analysis, all randomized patients will be analysed in the allocated group regardless of any protocol violations.
 |
| GCP Statement:              | 
This study will be conducted in compliance with the protocol, the current version of the Declaration of Helsinki, the ICH-GCP or ISO EN 14155 (as far as applicable) as well as all national legal and regulatory requirements.
                                                                                                                                                                                                                                                                                                                                                                                                                                                                                                                                                                                                                                                                                                                                                                                                                                                                          |

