### 3.7 Risks / Benefits

The main risk in this trial is virological failure on DTG + FTC dual therapy. In the ART Cohort Collaboration of 18 cohorts from Europe and North America including about 17900 patients, low level viremia measured between 50 and 199 copies/ml was weakly associated with virological failure (aHR 1.38, 95%CI 0.96-2.00) (85). We will measure HIV-1 RNA level in the plasma on a regular basis to monitor for low level viremia. Any patient with HIV-1 RNA  $\geq 100$  copies/ml will undergo an additional HIV-1 RNA measurement 14 days later ( $\pm 5$  days), as well as additional adherence session and review of concomitant medications and dolutegravir and emtricitabine plasma concentration measurements.

We will define virological failure as plasma HIV-1 RNA  $\geq 100$  copies/ml on two consecutive measurements. Any patient reaching virological failure will be assessed for genotypic resistance and pharmacogenetic analyses. This latest analysis will be only done in patients who are included in the SHCS and have also signed a consent form for genetic studies. In case of virological failure, the patient will undergo an additional medical visit with review of adherence, concomitant medications, discussion of results of DTG + FTC plasma concentration. Patients randomised in the DTG + FTC dual therapy arm will be switched to a standard cART regimen while waiting for results of genotypic resistance. Patients randomised in the continuing cART arm will await results of the genotypic results. In both cases, treatment will be adjusted according to genotypic resistance results. All failing patients will complete study procedures until week 48. Figure 3 presents the algorithm for the management of virological failure.

Any patient with HIV-RNA between 20 and 99 copies at any time of scheduled visits will have an additional HIV-RNA measurement after 6 weeks (+/-5 days).

Figure 3: Algorithm for the management of virological failure

[figure not shown]

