## 5. STUDY OUTCOMES

### 5.1 Primary Outcomes

The *first primary outcome* for the comparison between DTG + FTC dual therapy and standard cART is the proportion of patients maintaining HIV suppression defined as HIV-RNA <100 copies/ml throughout 48 weeks (+/- 21 days). A single blip defined as HIV-RNA <200 copies/ml during the study period is allowed as long as this value is followed by HIV-RNA <50 copies/ml.

The *second primary outcome* for the comparison between patient-centered and standard monitoring is the direct costs of the two study arms from the health care system perspective at week 48.

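### The per-protocol exception in 11.4.1 protects only confirmed virological failures, so some patients already known to have failed the primary outcome leave the per-protocol set

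*Protocol*

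**What the plan says.** **Primary outcome.** Section 5.1 defines success as HIV-RNA below 100 copies/ml throughout 48 weeks. The only relief is that "A single blip defined as HIV-RNA <200 copies/ml during the study period is allowed", provided the next value is below 50 copies/ml. Failing the outcome requires no confirmatory measurement.

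**Virological failure.** Section 3.7 sets the threshold at 100 copies/ml or more and continues "copies/ml on two consecutive measurements. Any patient reaching virological failure will be assessed". Section 7.4 uses the same two-consecutive-values rule for stopping DTG + FTC. The synopsis (Measurements and procedures) has two values of at least 100 copies/ml, 2 weeks apart. Section 9.2.2 describes patients failing treatment in the same two-value terms.

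**Per-protocol set, main text.** Section 11.4.1 excludes "patients who discontinue treatment prematurely (< 47 weeks), unless virological failure occurred before" and also "those who do not have HIV-1 RNA results at week 48 (+/-21 days), unless virological failure occurred before". It requires the per-protocol and intention-to-treat analyses to reach the same conclusion before non-inferiority is accepted.

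**Per-protocol set, synopsis.** Statistical Considerations excludes "patients who discontinue treatment prematurely for reasons other than death", patients below 80% adherence, and patients without a week-48 HIV-RNA result. Virological failure is not mentioned as an exception.

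**The concern.** The exception in 11.4.1 is evidently meant to keep patients whose failure was already observed when they stopped or went missing. It relies on a defined term that is narrower than failure of the primary outcome. A patient can therefore have a settled primary result, namely failure, and still be removed as if the outcome were unknown.

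The per-protocol analysis is one of two that must support the non-inferiority conclusion. A set that discards known failures is a less demanding test than the protocol intends. Where such patients are in the DTG + FTC arm, their removal makes the per-protocol difference look more favourable.

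**Working it through.** **Step 1. The definitions side by side.** All cases assume the patient then stops before week 47 or has no week-48 HIV-RNA.

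| HIV-RNA pattern before that point | Primary outcome (5.1) | Virological failure (3.7, 7.4) | Per-protocol set (11.4.1) |
|---|---|---|---|
| Two consecutive values ≥100, at least one ≥200 | Failed | Yes | Kept as failure |
| One value ≥200, no retest | Failed | No | Dropped |
| One value ≥200, retest <100 | Failed | No | Dropped |
| One value 100–199, next value 50–99 | Failed | No | Dropped |
| Two separate blips, each followed by <50 | Failed | No | Dropped |

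Under the synopsis rule the first row is dropped as well. Section 7.4 takes DTG + FTC patients off study drug at confirmed failure, so a literal reading of the synopsis would remove them.

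**Step 2. The plan's own figure.** Inputs from 11.2: 97% and 94% success, margin 12 points, one-sided 0.025, power 80%.

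n per arm = (1.960 + 0.842)² × (0.97×0.03 + 0.94×0.06) / (0.12 − 0.03)² = 7.849 × 0.0855 / 0.0081 = 82.85, rounded up to 83.

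This reproduces the stated 83 per group. At 92 per arm the planning rates imply about 92×0.03 = 2.8 cART failures and 92×0.06 = 5.5 DTG + FTC failures.

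**Step 3. Effect of dropping failures from the test arm.** The counts are assumptions chosen near the margin. The protocol's interval is a Mantel-Haenszel one stratified by monitoring type (11.4.2), which would need stratum counts. Two unstratified 95% intervals for the difference d = p_T − p_C serve as illustrations:

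- Wald: d − 1.96 × √[p_T(1−p_T)/n_T + p_C(1−p_C)/n_C]
- Newcombe: d − √[(p_T − l_T)² + (u_C − p_C)²], with l_T the lower and u_C the upper Wilson limit

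Newcombe example, 6 v 2 failures at 83 per arm: p_T = 77/83 = 0.9277, l_T = 0.8511, p_C = 81/83 = 0.9759, u_C = 0.9934. The limit is −0.0482 − √(0.0766² + 0.0175²) = −12.7%.

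Wald example, 8 v 3 failures at 92 per arm: d = 84/92 − 89/92 = −0.0543, SE = 0.0347. The limit is −0.0543 − 1.96×0.0347 = −12.2%.

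| Failures, DTG + FTC v cART | Dropped | Wald lower limit | Newcombe lower limit |
|---|---|---|---|
| 6/83 v 2/83 | 0 | −11.3% | −12.7% |
| 5/82 v 2/83 | 1 | −9.8% | −11.3% |
| 7/83 v 2/83 | 0 | −12.9% | −14.2% |
| 5/81 v 2/83 | 2 | −10.0% | −11.4% |
| 8/92 v 3/92 | 0 | −12.2% | −13.3% |
| 7/91 v 3/92 | 1 | −11.0% | −12.1% |

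One dropped failure moves the lower limit by 1.2 points (92 per arm) to 1.5 points (83 per arm, Wald), and the estimate itself by about 1.0 to 1.1 points.

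**Step 4. Size against an assumed share dropped.** Let q be the share of primary failures lost from the per-protocol set, equal in both arms. The protocol gives no value for q. At a true difference exactly at the margin (85% v 97%), the expected per-protocol difference is

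0.85/[0.85 + 0.15(1−q)] − 0.97/[0.97 + 0.03(1−q)].

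| q | Expected difference (points) | Per-protocol analysis alone passes (simulated, 92 per arm, Wald) |
|---|---|---|
| 0% | −12.0 | 3.9% |
| 5% | −11.5 | 5.0% |
| 10% | −11.0 | 6.6% |
| 20% | −10.0 | 10.9% |
| 30% | −8.9 | 17.8% |

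The 3.9% at q = 0 already exceeds 2.5% because of the simple Wald interval. The last column describes the per-protocol analysis alone, not the trial's conclusion.

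**The case against.** **Intention-to-treat is a safeguard.** It analyses all randomised patients and must agree with the per-protocol result. A reader might infer that the wording could by itself produce a false non-inferiority claim. It cannot: every failure dropped from the per-protocol set remains a failure under 5.1 in the intention-to-treat analysis. This stands and limits the consequence.

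**The group is small.** A value of 100 or more calls for a retest after 14 days (3.7), DTG + FTC is stopped at confirmed failure (7.4), and those who stop study drug are generally to complete procedures to week 48. Patients who re-suppress and stay on treatment remain in the set as failures. Losing 2 of 7 failures, as in one illustration, is a share no document supports. This also stands.

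**Direction.** A reader might infer that the lost failures come mainly from the test arm, since the trial is open-label and 7.4 lists stopping criteria for DTG + FTC only. That is plausible, but the virological criterion listed there is confirmed failure. Nothing documents that one unconfirmed value leads to stopping more often in one arm.

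**A one-patient reversal.** A reader might take the example of 6 v 2 at 83 per arm as showing that one patient changes the verdict. It does under Newcombe but not under Wald, where non-inferiority is already shown. The 8 v 3 example at 92 per arm behaves the other way round. Only the two-patient example reverses under both.

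**Confirmed failure is a respectable convention.** Single values can be transient, and the secondary time-to-loss outcome in 5.2 requires confirmation. But the primary outcome does not, and an exception meant to protect known primary failures should use the definition being analysed. Reading the term loosely in 11.4.1 would close the gap, yet the protocol gives it the two-value meaning each time it defines it.

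**Conclusion.** The mismatch is real and follows from the text alone. As written, 11.4.1 drops patients with a known but unconfirmed primary failure who stop before week 47 or lack a week-48 result. The synopsis, read literally, drops confirmed failures too, and so contradicts 11.4.1.

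The consequence is a weaker per-protocol check. It is not a route to a false conclusion unless intention-to-treat also passes. Per patient, the effect on the per-protocol lower limit is about 1.2 to 1.5 points for a dropped test-arm failure. This rests on 83 to 92 patients per arm, failure counts near the margin and unstratified intervals. How many patients are affected, and in which arm, cannot be derived from the protocol. No stated figure is wrong on this point; the sample size of 83 per group reproduces.

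**What to change.** In 11.4.1, replace both exceptions (early discontinuation and missing week-48 HIV-RNA) with: *unless the primary outcome (5.1) had already been failed on available HIV-RNA values*. Give the synopsis the same per-protocol rule, so that the two places agree.

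The exclusion for adherence below 80% in 11.4.1 has no failure exception either. Removing non-adherent patients is an ordinary purpose of a per-protocol set, but the authors should state whether a known primary failure is also meant to leave by that route.

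The cost is a short wording change in two places. It needs no new data and does not alter patient management. The per-protocol estimate may become slightly less favourable to DTG + FTC.

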Time to loss of virological response (TLOVR) will be graphically depicted by Kaplan-Meier curves, and evaluated by a univariable and multivariate Cox proportional Hazard model, adjusted for stratified for the type of monitoring and type of treatment.

Predictors of virological failure (nadir CD4 count, baseline HIV-DNA, zenith HIV-RNA, years since HIV infection, years of viral suppression, CD4/CD8 ratio, age, DTG and FTC plasma concentrations, pharmacogenetic analysis, any other relevant clinical or laboratory parameters) will be assessed using forward stepwise multiple logistic regression.

Economic analyses will be performed from the health provider perspective. A multiple linear regression model will be performed to compare the mean direct costs between the two monitoring strategies after adjustment for the treatment arm.

All analyses will be performed in the PP dataset and in the ITT dataset.

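### One per-protocol set serves both factors: the PP cost comparison drops patients for drug and HIV-RNA reasons, and the PP drug comparison drops patients for not receiving their allocated monitoring

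*Protocol*

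**What the plan says.** Section 11.4.1 names two analysis sets, one PP and one ITT, neither tied to a factor. Four kinds of criterion remove a patient from PP:

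- Stopping drug: "patients who discontinue treatment prematurely (< 47 weeks), unless virological failure occurred before".
- Adherence: "patients with a treatment adherence of less than 80% while on treatment".
- Missing endpoint: "those who do not have HIV-1 RNA results at week 48 (+/-21 days), unless virological failure occurred before".
- Major protocol deviation: failure to obtain consent, and "violation of any inclusion criteria, not receiving the allocated treatment or monitoring".

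The same section makes PP co-decisive for the drug question: "Per-protocol and intention-to-treat analyses should reach the same conclusion to consider DTG + FTC as non-inferior to standard treatment". ITT keeps all randomised patients in their allocated group.

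Section 11.4.2 describes the Mantel-Haenszel risk difference for the drug comparison and the linear regression of direct costs on monitoring arm. It then states: "All analyses will be performed in the PP dataset and in the ITT dataset".

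The synopsis (Statistical Considerations) defines PP differently. It lists premature discontinuation other than by death, adherence below 80%, and no week-48 HIV-RNA. It has no monitoring criterion and no exception for earlier virological failure.

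**The concern.** The trial asks two separate primary questions: non-inferiority of DTG + FTC to cART, and direct costs under patient-centered versus standard monitoring. A PP set is meant to show the effect in patients who followed the intervention being compared. With one shared set, a departure on either factor removes a patient from both comparisons.

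For the drug question, a patient who took the allocated drugs and has a complete HIV-RNA series is dropped for not receiving the allocated monitoring. Because PP must agree with ITT, that exclusion enters an analysis on which the non-inferiority conclusion depends.

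For the cost question, a patient who received the allocated monitoring is dropped for stopping a drug, for pill-taking or for one absent laboratory result. These events occur after randomisation and may be related to cost, so the exclusion can select patients on something linked to the outcome.

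**Working it through.** **Which criterion belongs to which question**

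| PP criterion (11.4.1) | Drug question | Cost question |
|---|---|---|
| Drug stopped before 47 weeks, no earlier virological failure | relevant | not adherence to monitoring |
| Adherence below 80% | relevant | not adherence to monitoring |
| No week-48 HIV-RNA, no earlier virological failure | relevant (endpoint) | not needed to measure cost |
| Allocated treatment not received | relevant | not adherence to monitoring |
| Allocated monitoring not received | not adherence to drug | relevant |
| Consent, inclusion criteria | relevant | relevant |

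**Cost side**

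1. Section 9.2.1 takes costs from the participants' health insurance and from trial accounting. Neither source needs a week-48 HIV-RNA or 80% adherence.
2. Section 7.4 has DTG + FTC patients stop study drug for, among other reasons, serious adverse events that require it, while in general remaining in the study to week 48. Hospitalisation is one criterion of a serious adverse event (10.1.1) and a cost item (9.2.1). So an event that creates cost can also remove the patient from the PP cost analysis.
3. Neither the share excluded nor the cost of those excluded is given in the protocol, so no bias in CHF can be calculated.

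**Drug side: the plan's own figure first**

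Inputs from section 11.2: 97% on cART, 94% on DTG + FTC, margin 12 points, one-sided 0.025, power 80%.

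n = (1.960 + 0.842)² × (0.97×0.03 + 0.94×0.06) / (0.12 − 0.03)² = 7.85 × 0.0855 / 0.0081 = 82.9, so 83 per arm, as stated. Inflation: 166/0.9 = 184.4; the plan uses 184, or 92 per arm.

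**Illustration (the exclusion shares are assumptions)**

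Power = Φ(0.09 / √(0.0855/n) − 1.960)

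| Patients per arm in PP | Power |
|---|---|
| 92 (no exclusion) | 84% |
| 83 (92 less a total of 10%) | 80% |
| 78.8 (83 less 5%) | 78% |
| 74.7 (83 less 10%) | 76% |
| 70.5 (83 less 15%) | 73% |

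The last three rows assume that the whole 10% allowance has already been used and that monitoring non-receipt comes on top.

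**Cost power, for scale**

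With 92 per group, SD CHF 8,000 and a 10% difference (CHF 2,500), the t-test has 55.9% power; the plan says about 55%. A total PP exclusion of 10% (83 per group) gives 51.7%. How much of such an exclusion would come from drug-side criteria is not known.

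**The case against.** Several points on the other side stand.

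- ITT keeps every randomised patient, and the rule that PP and ITT must agree covers only non-inferiority. A reader might infer that the primary cost result is biased or no longer randomised. The protocol does not support that: only the PP cost analysis is affected, and no cost conclusion depends on it.
- Every PP set selects on events after randomisation. A monitoring-specific set would do so too, through receipt of monitoring. Separate sets reduce the selection and do not remove it.
- The criteria are narrower than they first appear. Patients with earlier virological failure stay in despite stopping drug or lacking the week-48 result, and the monitoring criterion is a major deviation, not receiving the allocated monitoring. Small departures do not exclude.
- It would be too strong to call monitoring deviations unrelated to drug-taking. Patient-centered monitoring covers drug delivery and visit format, although section 6.1 says that interventions potentially related to adherence are identical between arms.
- Week-48 HIV-RNA is part of the schedule in both monitoring arms, at the same place (section 8.1.1, Table 1), so the design gives no reason to expect its absence to differ by arm.
- It is tempting to put a CHF figure on the cost bias. A 5-point difference in exclusions and an excess of CHF 10,000-20,000 per excluded patient would shift the difference by 0.05 × 10,000 = 500 to 0.05 × 20,000 = 1,000. Neither input is in the protocol, and the sign is open because early leavers may have lower recorded costs. The result is also below one standard error, 8,000 × √(2/92) ≈ CHF 1,180.

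Two arguments do not remove the point. The interaction test and four-arm fallback use both factors, which gives a shared set some rationale, but only for those analyses; the pooled comparisons do not need it. Section 11.4.6 leaves detail to a SAP, but here the protocol itself fixes the shared set and applies it to everything.

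**Conclusion.** The point holds in limited form. Section 11.4.1 fixes one PP set for two different questions, and section 11.4.2 applies it to all analyses. This makes the PP analysis less well targeted for each factor, and for the drug factor that analysis is co-decisive. The synopsis and section 11.4.1 also disagree on whether monitoring is a PP criterion.

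The consequence is probably modest, but its size cannot be derived from the protocol. The power range of 78% to 73% rests on assumed exclusions of 5% to 15% on top of a fully used allowance; a total exclusion of 10% from 92 per arm leaves about 80%. For costs, the documents support only that patients with possibly complete cost data are dropped for reasons that may be related to cost. They do not support a stated bias or an invalid ITT cost comparison. The change is worth making because it costs almost nothing and settles the inconsistency.

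**What to change.** Define PP by factor in section 11.4.1 and bring the synopsis into line:

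- **PP-drug**, for non-inferiority and the other drug comparisons: keep the present consent, eligibility, drug-side and HIV-RNA criteria, including the exception for earlier virological failure, and delete the reference to monitoring.
- **PP-monitoring**, for costs and acceptability: require consent, eligibility and receipt of the allocated monitoring. Do not exclude for drug discontinuation, pill adherence or a missing week-48 HIV-RNA.

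State in section 11.4.2 which set serves which comparison. If a PP version of the interaction test or of the four-arm fallback is wanted, it can use the patients who belong to both sets. Leave ITT as it is.

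The cost is a few lines in section 11.4.1 and the synopsis, repeated in the SAP, and one more analysis flag. No new data are needed. The change should be made before the data are analysed.
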